**4. Economic feasibility evaluation**

Economic feasibility will be evaluated on patients who participated in the clinical trial at least once since visit 2. The economic endpoint to assess cost-effectiveness will be incremental cost-utility ratio, which will be calculated based on the difference in cost and quality-adjusted life year between the experimental and control groups. Quality-adjusted life year will be calculated using EQ-5D measured at the time of visit.

$$\text{ICUR}=\frac{\text{Total Cost}\;(\text{treatment group})-\text{Total Cost}\;(\text{control group})}{\text{Quality-adjusted life year}\;(\text{treatment group})-\text{Quality-adjusted life year}\;(\text{control group})}$$

A. Time horizon

Basic time horizon for analysis will be 4 or 8 weeks. If long-term follow-up beyond 8 weeks is required, the Markov model will be used. Transition probabilities will be estimated based on clinical data collected over 8 weeks. In addition, if the time horizon exceeds 12 months, the unit of cost will be in Korean currency unit (won) for specific years, and a discount rate of 4.5% will be applied based on the economic feasibility evaluation guidelines of the Health Insurance Review and Assessment Service.

B. Analysis perspective

Societal perspective and restricted societal perspectives will be applied to include direct nonhealthcare, direct nonhealthcare, and lost productivity costs.

C. Sensitivity analysis

Deterministic sensitivity analysis will be conducted on all possible parameters and a tornado diagram will be presented. Probabilistic sensitivity analysis will be conducted using the distribution and representative values of all possible parameters. In addition, bootstrap using individual patient level data will be conducted to present the distribution of the economic feasibility evaluation effect index and 95% confidence intervals.

D. Assumptions for missing values

Last-Observation-Carried-Forward analysis method, a conservative method of underestimating missing values in cases where the result is expected to improve over time within the time horizon, is widely used to correct for missing values in clinical studies. Herein, the Last-Observation-Carried-Forward method will be used to assume missing values. In other words, if the patient is withdrawn from the study or completes treatment early, the last measured values will be used for all remaining visits to conduct analysis.

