### Sample size calculation

2.3

This is a practical clinical study to assess the effects NBT and deeply inserted acupotomy combination treatment on lumbosacral radiculopathy.

In a previous pilot RCT that compared the therapeutic effects of deeply inserted acupotomy and general acupuncture in lumbar disc herniation patients,^[14]^ considering a 20% drop-out rate, a total of 50 patients (25 each in the acupuncture and deeply inserted acupotomy groups) were included.

In another RCT that compared the effects of deeply inserted acupotomy and general acupuncture in lumbar disc herniation patients,^[15]^ a total of 40 patients (20 each in the acupuncture and deeply inserted acupotomy groups) were included.

The phase 1 preliminary clinical study that will be conducted aims to estimate the mutual effects of NBT and deeply inserted acupotomy combination treatment and assess whether the combination treatment is effective and safe compared with conventional treatment. Thus, the study must be conducted with a minimum number of patients within the limit that satisfies the study purpose. Currently, there is no previous study that has provided the same intervention. Therefore, based on previous studies that provided similar treatment interventions and involved disease groups as in our study, 20 patients were included in each group. Considering a dropout rate of 20%, a total of 50 patients (25 patients in each group) was set as the target sample size.

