### Recruitment, randomization, blinding, and nonblinding

2.6

Advertisements for patient recruitment will be posted on the Catholic Kwandong University, International St. Mary's Hospital's bulletin boards, along with posters, banner advertisements, and internet cafes. All advertisements will be run after institutional review board (IRB) approval.

Individuals who provide written consent to participate in the study will be assigned a screening number, according to the order of the outpatient visit at screening. Unblinded sub-investigators, who do not influence the research results and analysis, will refer to the randomization list that has been prepared by a commissioned professional statistician, and assign participation numbers. Participants will be allocated to the NBT group and the acupotomy + NBT group in a ratio of 1: 1. A block randomization table will be generated by an independent statistician and patients will be assigned to one of 2 groups according to the randomization table. Screening numbers, randomization numbers, and initials assigned to each participant will be used as subject identification codes to identify the participant until the end of the clinical trial.

The NBT used in this study is not a clinical investigational product and does not require allocation concealment, since it is administered to all groups. Moreover, it is impossible to blind the investigator and the participant in each group due to the nature of the study intervention, which is based on the contact between the patient and the medical staff. Instead, the investigator maintains blinding to prevent bias in evaluating the participant. After the clinical trial is completed, all clinical report forms (CRFs) will be collected, the database process terminated, and unblinding performed, if required for statistical analysis. Moreover, if it is deemed necessary to confirm the subject group due to an emergency situation during the clinical trial, the randomization code will be disclosed only to the participant, according to the principal investigator's discretion. If it is not possible to consult with the principal investigator and the situation is urgent, the randomization code of the subject will be disclosed after consultation with the randomization code officer. If unblinding is performed, the documentation of the reason for the unblinding will be retained, and the participant with the disclosed randomization code will not be able to continue the trial.

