**Efficacy evaluation**
In the efficacy evaluation, ITT will be treated as the main analysis group, and PP sets will be treated as the secondary analysis group. All statistical analysis will be conducted as two-sided tests with a significance level of 5%. Two-sided 95% confidence interval will be presented. Descriptive statistics will be presented for each treatment group and visit. Descriptive statistics and 95% confidence intervals will be presented for differences between the baseline and each visit.

Among efficacy evaluation variables, missing values of continuous variables will be analyzed using baseline observation carried forward correction.

A. Analysis of primary endpoints

For symptoms of lumbosacral radiculopathy at each measurement time point, descriptive statistics (number of patients, mean, and standard deviation) of the ODI score and changes in ODI at the end of treatment (4 weeks) and follow-up (8 weeks) compared with the baseline will be presented.

Paired *t*-test or Wilcoxon's signed ranked test will be conducted for intra-group changes in ODI at the end of treatment (week 4) compared with the baseline (0) depending on the satisfaction of normality. An analysis of variance model that includes changes in ODI at the end of treatment compared with the baseline as effects and baseline ODI as covariates will be used to evaluate the effects in the treatment group compared with the control group. Differences in least-square mean between treatment and control groups will be calculated, and two-sided 95% confidence interval and *P* value for the differences will be presented.

B. Analysis of secondary endpoint

Changes in ODI at follow-up (8 weeks) compared with baselineAssessment of subjective pain intensity in patients with lumbosacral radiculopathy-Lumbosacral radiculopathy pain will be divided into lower back and lower extremity pain using NRS, MPQ, and K-RMDQAssessment of quality of life related to lumbosacral radiculopathy-Evaluation of overall quality of life using EQ-5D. The same analysis methods for primary endpoints will be used to analyze secondary endpoints

C. Exploratory efficacy evaluation

Evaluation related to additional NBT or surgery after completion of the study

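### The cost-utility ratio uses a plain between-arm QALY difference with no stated adjustment for week-0 EQ-5D; adjusting for it would be a free gain in precision

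*Protocol article*

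**What the plan says.** Section 2.9, item 4 (Economic feasibility evaluation) names the ICUR as the economic endpoint, "which will be calculated based on the difference in cost and quality-adjusted life year between the experimental and control groups". The equation printed there is treatment-arm total cost minus control-arm total cost, over treatment-arm QALY minus control-arm QALY. On the QALY itself it says only: "Quality-adjusted life year will be calculated using EQ-5D measured at the time of visit". The horizon is short: "Basic time horizon for analysis will be 4 or 8 weeks". The section goes on to set out perspective, deterministic and probabilistic sensitivity analyses, a patient-level bootstrap and a missing-data rule. None of these mentions baseline utility.

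The baseline value exists. Table 1 and Section 2.8.6 schedule EQ-5D at weeks 0, 2, 4 and 8.

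The efficacy part of Section 2.9 handles baseline differently. The primary model has "baseline ODI as covariates", and the same methods are to be used for the secondary endpoints, EQ-5D among them. The natural reading is that EQ-5D as a clinical endpoint is adjusted for its own baseline.

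On size, Section 2.3 states that "a total of 50 patients (25 patients in each group) was set as the target sample size". Section 2.6 describes blocked 1:1 allocation and mentions no stratification.

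**The concern.** Week-0 utility enters each patient's QALY twice: directly, as the first point of the area under the curve, and indirectly, because patients who start with higher utility tend to have higher utility later. The arm that happens to start better is therefore credited with QALYs that treatment did not produce. As written, the same instrument in the same patients is baseline-adjusted as a clinical outcome but not in the cost-utility analysis, and no reason is given.

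This matters because cost-effectiveness is part of the hypothesis in Section 1.1 and because the denominator must be very small over 4 or 8 weeks. A ratio with a small, noisy denominator is unstable, and its sign can change by chance.

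**Working it through.** **The plan's own figure.** Section 2.3 takes 20 per arm from earlier trials and allows for 20% dropout: 20 / (1 − 0.20) = 25 per arm, 50 in total. This reproduces. No effect size, SD or power is given.

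**Inputs from the document.** EQ-5D at weeks 0, 2, 4 and 8; 25 per arm (20 after the assumed dropout); horizon 4 or 8 weeks.

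**Assumptions, not in the document.** Trapezoid QALYs; utility SD σ = 0.20 (range 0.10 to 0.30); the same correlation ρ between any two visits, 0.3 to 0.7.

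**Weights.** Over 8 weeks the trapezoid rule weights weeks 0, 2, 4 and 8 by 1/8, 2/8, 3/8 and 2/8. The sum of squared weights is 18/64 = 0.28125.

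**Formulas**, for average utility over the horizon in units of σ²:
- variance V = ρ + (1 − ρ) × 0.28125
- covariance with week 0: C = 1/8 + ρ × 7/8
- share explained by baseline: R² = C²/V
- unadjusted SE of the QALY difference = σ × √V × √(2/25) × 8/52
- adjusted SE = unadjusted SE × √(1 − R²)
- SE of the baseline difference = 0.20 × √(2/25) = 0.0566
- QALY shift for a one-SE baseline imbalance = 0.0566 × C × 8/52

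| ρ | V | C | R² | SE unadjusted | SE adjusted | Reduction | One-SE shift |
|---|---|---|---|---|---|---|---|
| 0.3 | 0.4969 | 0.3875 | 0.302 | 0.0061 | 0.0051 | 16% | 0.0034 |
| 0.5 | 0.6406 | 0.5625 | 0.494 | 0.0070 | 0.0050 | 29% | 0.0049 |
| 0.7 | 0.7844 | 0.7375 | 0.693 | 0.0077 | 0.0043 | 45% | 0.0064 |

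R² and the percentage reduction do not depend on σ. Across σ from 0.10 to 0.30 and the same range of ρ, the one-SE shift runs from 0.0017 to 0.0096 QALY.

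**Scale.** Suppose treatment raises utility by 0.05 at weeks 2, 4 and 8 (an assumption). Week 0 precedes treatment, so its 1/8 weight contributes nothing: 0.05 × 7/8 × 8/52 = 0.0067 QALY. At ρ = 0.5 a one-SE imbalance (0.0049) is about 73% of that, and a 1.96-SE imbalance (0.0096) exceeds it.

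**How common such imbalances are.** With 25 per arm the SE of the baseline difference is √(2/25) = 0.283 SD. An absolute imbalance above 0.3 SD has probability 29%, and above 0.5 SD 8%. With 20 per arm the figures are 34% and 11%.

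**Wrong sign.** In 20,000 simulated trials (25 per arm, σ = 0.20, ρ = 0.5, the 0.05 gain above), the QALY difference was negative in 17% of trials unadjusted and 9% adjusted. The simulated SEs, 0.0070 and 0.0050, match the formulas.

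**Four-week horizon.** The weights are 1/4, 1/2 and 1/4, so week 0 carries a quarter of the area directly. At ρ = 0.5, R² is 0.568 and the SE falls from 0.0036 to 0.0024. A one-SE imbalance shifts the difference by 0.0027 QALY, and the 0.05 gain is worth 0.05 × 3/4 × 4/52 = 0.0029.

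**The case against.** The strongest reply is that the quoted sentence and equation are the textbook definition of an ICUR and do not name an estimator. A regression-adjusted difference would fit the same equation. The article never calls the difference unadjusted, and a fuller protocol or analysis plan might feed adjusted QALYs into it. This stands in part: a reader might infer that the plan has deliberately ruled out adjustment, and the document does not say that. What remains is that the article prints the comparison, goes on to detail the sensitivity analyses, bootstrap and missing-data rule, and puts no baseline term anywhere, although it states one for efficacy.

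A reader might also infer that the economic result would be biased or invalid. It would not be. Randomisation makes the unadjusted difference unbiased over repeated allocations, and the patient-level bootstrap would carry the baseline variation into the interval. The bootstrap would not narrow that interval or remove the realised imbalance from the point estimate.

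Two further extensions are not supported. The benefit should not be expressed as power, because the economic section plans no hypothesis test of QALYs. Nor is there a matching case on costs. Week-0 cost is collected, but the text gives no recall period, does not say that it enters the total, and offers nothing from which the gain from adjustment could be judged.

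Finally, Section 2.3 calls this a preliminary study, and small numbers will leave the ICUR unstable even after adjustment. That is true: 9% wrong-sign differences is still a sizeable share. It does not argue against a gain that costs nothing.

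**Conclusion.** The point holds as a free improvement, not as an error of validity. As printed, the ICUR denominator is a plain arm difference in QALYs with no stated use of the week-0 EQ-5D already collected. That makes it needlessly imprecise and, conditional on the imbalance that occurs, shifted by chance. The material range for 25 per arm over 8 weeks is an SE reduction of about 16% to 45% (29% at ρ = 0.5), and a shift of 0.0034 to 0.0064 QALY per one-SE imbalance at a utility SD of 0.20. These sizes rest on the assumed trapezoid rule, SD and equal correlation. The direction does not depend on the exact values, provided that baseline and later utility are positively correlated.

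**What to change.** In Section 2.9, item 4, state that incremental QALYs will be the arm coefficient from a linear regression of each patient's QALY on treatment arm and week-0 EQ-5D utility. State also that this coefficient is the ICUR denominator, that the regression is refitted within each bootstrap resample, and that the unadjusted difference is reported descriptively. The cost difference in the numerator can stay as it is.

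The cost is a sentence or two of text and one regression. It needs no new data, patients or visits. It should be fixed before results by arm are seen, so that the choice between the two estimates is not made after the fact.

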# Exploratory evaluation is not conduced for patients who have completed treatment early. For patients who dropped out of the study, exploratory evaluation is conducted after 4 weeks from dropping out (exploratory effectiveness evaluation for dropout participants can be conducted through telephone counseling instead of in-person visits).

∗∗ Evaluation of direct non-healthcare, direct non-healthcare, and lost productivity costs.

†† Those patients who reported adverse reactions will complete EQ-5D by recalling time of adverse events.

Patients who undergo 1 NBT and show continued symptoms (patient's subjective pain improvement is less than 50% after the procedure or the numeric rating scale (NRS) score being 5 or higher) will undergo screening at 1 week after the first procedure. For screening, demographic information, medical history, physical examination, vital signs, questionnaire survey, laboratory test, and selection/exclusion criteria will be evaluated. Randomization and group allocation will be performed at screening and baseline. Fifty patients will be enrolled and randomly divided into 2 groups. Patients who are judged suitable for the study after the screening test and voluntarily agree to participate will be randomly assigned to either the NBT single treatment group (usual care group) or NBT + deeply inserted acupotomy treatment group in a 1:1 ratio (Fig. 1). Thereafter, the randomly assigned patients will undergo primary and secondary outcome evaluations and economic evaluation.

The NBT + deeply inserted acupotomy group will receive 8 acupotomy treatments (at visits 2, 3, 5, 6, 7, 8, 10, and 11) for 4 weeks as well as additional 2 NBTs (at visits 4 and 9) for 4 weeks. Then, the group will be followed-up for 4 weeks after the intervention treatment. The standard care group will undergo two NBTs (at visits 2 and 4) for 4 weeks and will be followed-up for 4 weeks after the intervention treatment. Primary and secondary outcomes, economic evaluation, and assessment of drug administration history will be conducted at visits 1, 6, and 11, and at the end of follow-up. To evaluate safety, evaluation of adverse events, vital signs, and economic feasibility will be conducted at every visit from visit 2 to visit 12. Laboratory tests will be conducted only at screening.

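### A bootstrap 95% interval taken on the ICUR would not rank results by value for money if the QALY difference straddles zero, which is plausible with 25 per arm over 8 weeks

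*Protocol article*

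**What the plan says.** Cost-effectiveness is part of the hypothesis in section 1.1 (Objective). Section 2.9, item 4 (Economic feasibility evaluation) states: "The economic endpoint to assess cost-effectiveness will be incremental cost-utility ratio". It prints the formula as the difference in total cost divided by the difference in QALYs. On the denominator it says: "Quality-adjusted life year will be calculated using EQ-5D measured at the time of visit". Section 2.8.6 places those EQ-5D measurements at 0, 2, 4 and 8 weeks. On the horizon: "Basic time horizon for analysis will be 4 or 8 weeks".

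Under C (Sensitivity analysis) the article plans deterministic and probabilistic analyses, and adds that "bootstrap using individual patient level data will be conducted to present the distribution of the economic feasibility evaluation effect index and 95% confidence intervals". It does not name the index or the interval method. The ICUR is the only economic index it defines. It states no rule for a QALY difference near or below zero.

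Section 2.3 sets the size by precedent: "a total of 50 patients (25 patients in each group) was set as the target sample size".

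**The concern.** The ICUR has an estimated quantity in its denominator. Over 8 weeks that quantity is small, and with 25 per arm it is imprecise. If some bootstrap replicates give a positive QALY difference and others a negative one, the ratio passes through infinity and changes sign. Sorting the replicates by the size of the ratio then mixes opposite conclusions, and limits taken from the sorted list do not run from worse to better value for money.

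At stake is the uncertainty statement for the only economic endpoint. A finite pair of limits could be published and read as a range of cost per QALY when it is not one.

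**Working it through.** **Ordering.** Let c and q be positive amounts of money and QALYs. A replicate that is dearer and worse gives (+c)/(−q) = −c/q. A replicate that is cheaper and better gives (−c)/(+q) = −c/q. The ratio is the same and the conclusions are opposite. Positive ratios have the same problem: dearer and better, or cheaper and worse. Even among cheaper-and-better replicates, a larger q moves the ratio towards zero while a larger saving moves it away, so its size does not rank them. This follows from the printed formula alone.

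**Sample size.** The plan's own figure reproduces: 20/(1 − 0.20) = 25 per arm. The article gives no effect size, SD or power, for utility or for any other outcome. Last observation carried forward keeps up to 25 per arm in the economic analysis.

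**Assumptions, none from the article.**
- Utility SD σ = 0.10-0.20 at each visit.
- Correlation ρ = 0.5-0.7 between any two visits.
- Utility gain d: zero at baseline, d/2 at week 2, d at weeks 4 and 8.
- No baseline adjustment, since the formula shows none.

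**QALY difference.** The trapezoid rule on weeks 0, 2, 4 and 8 gives weights of 1, 2, 3 and 2 weeks. They sum to 8, so a patient in full health accrues 8/52 = 0.154 QALY. The expected difference is d × (2 × ½ + 3 + 2)/52 = 6d/52. For d = 0.05 this is 0.0058. With no gain at week 2 it would be 5d/52 = 0.0048, so the week-2 assumption is the more favourable one.

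**Standard error.** SD of a patient's QALY = σ × √[(1 − ρ) × 18 + ρ × 64]/52, where 18 is the sum of squared weights and 64 is the square of their sum. SE of the difference = SD × √(2/25).
- Smallest: σ = 0.10, ρ = 0.5: SD = 0.10 × √41/52 = 0.0123, SE = 0.0035.
- Largest: σ = 0.20, ρ = 0.7: SD = 0.20 × √50.2/52 = 0.0273, SE = 0.0077.

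**Chance that the 95% interval for the QALY difference includes zero.** With z = difference/SE, this is Φ(1.96 − z) − Φ(−1.96 − z). It is also the chance that a Fieller interval for the ICUR is unbounded. For d = 0.05, z runs from 0.75 to 1.66, which gives 88% down to 62%.

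| Gain d | QALY difference | Unadjusted | Baseline-adjusted |
|---|---|---|---|
| 0.03 | 0.0035 | 83-93% | 63-89% |
| 0.05 | 0.0058 | 62-88% | 23-79% |
| 0.08 | 0.0092 | 24-78% | 1-54% |
| 0.10 | 0.0115 | 9-68% | 0-36% |

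The adjusted column replaces the bracket by (1 − ρ) × 17 + ρ(1 − ρ) × 49, which is 20.75 at ρ = 0.5 and 15.39 at ρ = 0.7. The SE is then 0.0021-0.0050.

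With 20 per arm and no adjustment, the figures are 68-90% for d = 0.05 and 16-73% for d = 0.10. On the 4-week horizon the weights are 1, 2 and 1, so d = 0.05 is worth 2 × 0.05/52 = 0.0019. With ρ = 0.5 and σ = 0.15-0.20, the interval includes zero in 89-92% of trials.

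**Bootstrap check.** 500 simulated trials with 1,000 resamples each, 25 per arm, ρ = 0.5, σ = 0.10-0.20. More than 2.5% of resamples lay on each side of zero in 80-89% of trials for d = 0.03, 57-85% for 0.05 and 8-59% for 0.10. For d = 0.05 the median share of negative QALY differences was 4%, 13% and 21% at σ = 0.10, 0.15 and 0.20. Coverage of the percentile interval for the ICUR was 0.94-0.98. The article gives no cost data, so the costs in this simulation are assumed as well.

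**The case against.** The text does not say that percentiles of the ratio will be taken. It names no interval method, and its plural wording would also fit separate intervals for incremental cost and incremental QALYs. This stands: the point is conditional on the interval being taken on the ratio, which is the natural reading but still an inference.

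The article is a condensed account, and a full protocol or analysis plan may include net benefit, a cost-effectiveness plane or an acceptability curve. This also stands, so their absence is not the point. The point is the combination the article does fix: a ratio as sole endpoint, with a 95% interval for an index that is most naturally that ratio.

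A reader might infer that such an interval has no meaning, or is not a confidence interval for anything. The documents and the check do not support that. Simulated coverage stayed near nominal, and when the QALY difference is clearly on one side of zero the limits can be interpreted.

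A reader might also infer that a straddling denominator is the most likely outcome of this trial. The article gives no utility SD, correlation or expected gain, and the unadjusted chance runs from 9% to 93% over the ranges shown. Frequency is therefore not established.

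Finally, the bootstrap sits under sensitivity analysis in a study described as preliminary, and the primary endpoint is the ODI. That limits the weight of the point but does not remove it.

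**Conclusion.** The concern holds in conditional form. If the bootstrap interval is taken on the ICUR and the resampled QALY differences lie on both sides of zero, the limits cannot be interpreted as a cost-effectiveness statement. The defect is one of ordering and interpretability, not necessarily of coverage.

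Under the stated assumptions, straddling is common for gains of 0.03 to 0.05 without baseline adjustment. It becomes uncommon for a gain near 0.10 with a small SD, or with strong baseline adjustment. The algebra of the ratio needs no assumption; the percentages rest entirely on the assumed SD, correlation and gain pattern. The point concerns a secondary objective and is worth correcting before analysis.

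**What to change.** In section 2.9, item 4:
- Keep the ICUR as a point estimate, and report incremental cost and incremental QALYs separately, each with its 95% confidence interval.
- Base the uncertainty statement on incremental net monetary benefit, λ × (QALY difference) − (cost difference), with its bootstrap 95% interval. Fix the willingness-to-pay value λ, or a range of values, before analysis. This quantity has no denominator and, for a given λ, a higher value always means better value for money.
- Show the cost-effectiveness plane and the acceptability curve from the same replicates.
- State which index the bootstrap interval refers to.

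The cost is a change of wording. The patient-level replicates already planned supply every quantity, with no extra patients, visits or data. The one real demand is that a threshold or range be named in advance.

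### The economic analysis carries the last value forward without exempting costs, and it fills a missing EQ-5D differently from the efficacy analysis

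*Protocol article*

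**What the plan says.** The economic endpoint in section 2.9 is an incremental cost-utility ratio, "calculated based on the difference in cost and quality-adjusted life year between the experimental and control groups". On the denominator the plan says that "Quality-adjusted life year will be calculated using EQ-5D measured at the time of visit". On the horizon it says: "Basic time horizon for analysis will be 4 or 8 weeks".

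Part D of the same evaluation deals with missing data: "Herein, the Last-Observation-Carried-Forward method will be used to assume missing values". The method is described as "a conservative method of underestimating missing values in cases where the result is expected to improve over time within the time horizon". The rule is then spelled out: "if the patient is withdrawn from the study or completes treatment early, the last measured values will be used for all remaining visits". Costs are neither named nor exempted.

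Section 2.8.6 has EQ-5D, direct medical cost, direct nonmedical cost and productivity loss all recorded at 0, 2, 4 and 8 weeks. It takes the acupotomy cost from institutional data. Table 1 also ticks the cost evaluation and the secondary endpoints, EQ-5D among them, in the early-termination column.

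The efficacy part of section 2.9 uses a different rule: "missing values of continuous variables will be analyzed using baseline observation carried forward correction". EQ-5D is a secondary efficacy endpoint there, analysed in the same way as the primary endpoint.

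**The concern.** EQ-5D is a state at a point in time. A cost is a flow over an interval, and it changes when treatment stops. Table 1 places the last trial treatment at days 26-28, so nobody has a planned session between weeks 4 and 8. If a cost from a treatment interval is copied into later visits, the total includes spending that did not occur. The argument that the method is conservative concerns a result that improves with time and gives no support for using it on costs.

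The rule expressly covers patients who finish treatment early because they have improved, and their treatment costs should fall. An acupotomy excess would arise only in the combination arm, so it would not cancel from the cost difference.

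The second issue is consistency. The same missing EQ-5D value receives one number in the efficacy analysis and another in the cost-utility analysis of the same trial. Cost-effectiveness is part of the hypothesis in section 1.1, so both issues bear on a stated objective.

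**Working it through.** **The plan's own figure.** Section 2.3 starts from 20 per group and allows 20% dropout: 20 / (1 − 0.20) = 25 per group, 50 in total. This reproduces. The article gives no unit costs, utilities or early-termination rate.

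**Inputs for the combination arm (Table 1 and section 2.2).**
- Acupotomy: visits 2, 3, 5 and 6 up to the week-2 evaluation (4 sessions); visits 7, 8, 10 and 11 up to week 4 (4); none in weeks 4-8. Planned total 8.
- Nerve block therapy (NBT): visit 4 (1), visit 9 (1), none in weeks 4-8. Planned total 2.

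**Assumptions.** Each recorded cost covers the interval since the previous evaluation, including that day's session. It is carried forward unscaled. Patients who do not stop receive all planned sessions.

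**Per patient, 8-week horizon.**
- Last measured at week 2: acupotomy charged 4 + 4 + 4 = 12, received 4; NBT charged 1 + 1 + 1 = 3, received 1.
- Last measured at week 4: acupotomy charged 4 + 4 + 4 = 12, received 8; NBT charged 3, received 2.

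Both charges exceed the planned maximum of 8 and 2.

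**Arm mean.** With k stoppers among 25, the mean is [(25 − k) × 8 + k × sessions per stopper] / 25.

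| Stoppers, last measured | Horizon | Charged | Given | Excess |
|---|---|---|---|---|
| 5, week 2 | 8 weeks | (160 + 60)/25 = 8.80 | (160 + 20)/25 = 7.20 | +22% |
| 3, week 2 | 8 weeks | (176 + 36)/25 = 8.48 | (176 + 12)/25 = 7.52 | +13% |
| 1, week 2 | 8 weeks | (192 + 12)/25 = 8.16 | (192 + 4)/25 = 7.84 | +4% |
| 5, week 4 | 8 weeks | (160 + 60)/25 = 8.80 | (160 + 40)/25 = 8.00 | +10% |
| 5, week 2 | 4 weeks | (160 + 40)/25 = 8.00 | (160 + 20)/25 = 7.20 | +11% |

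Five of 25 borrows the 20% dropout allowance. That allowance is not a forecast of early termination, which section 2.8.7.2 does not count as withdrawal.

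With five stoppers at week 2, the NBT excess is 5 × 2 / 25 = 0.4 per patient. It cancels between arms if stopping is equal.

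**EQ-5D.** Take an early terminator with utility u0 at baseline and a higher u2 at week 2, and nothing later. The efficacy rule sets week 8 to u0, a change of u0 − u0 = 0. The economic rule sets weeks 4 and 8 to u2, so the gain u2 − u0 is held to week 8. The patient shows no benefit in one analysis and a sustained benefit in the other.

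**The case against.** The article never says outright that costs are carried forward, and its justification speaks of a result that improves, which suggests that the authors had utility in mind. Acupotomy cost comes from institutional data, so it could be counted from sessions given and would then not be missing. Table 1 schedules a cost and EQ-5D evaluation at early termination, so a stopper's last value may cover a short interval with few or no sessions. These points stand. They make the excess smaller than the illustration, possibly zero for acupotomy itself. They do not remove the problem: part D does not limit the rule, no other rule for missing costs is given, and transport, time, outpatient and productivity costs do not come from institutional acupotomy records.

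Three stronger readings are tempting but not supported.
- A reader might infer that the ratio is biased against the combination. Nothing shows which arm will have more or earlier stoppers, and costs of care sought elsewhere after withdrawal could be understated instead.
- A reader might infer from the perspective sentence, which is to "include direct nonhealthcare, direct nonhealthcare, and lost productivity costs", that acupotomy cost is left out. Section 2.8.6 lists it first under direct medical cost and the formula uses total cost, so the repeated term is a wording slip.
- A reader might fault the lack of adjustment of QALYs for baseline EQ-5D. The article is silent on this, and such detail may properly sit in an analysis plan that is not shown.

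**Conclusion.** The concern holds in a limited form. The economic missing-data rule is unrestricted, its rationale does not extend to costs, and applied literally it would place treatment-period costs in weeks without treatment. In the scenarios shown, mean acupotomy sessions charged are overstated by 4% to 22%, with the upper figure requiring a fifth of the arm to be last measured at week 2. All of these rest on interval costs carried unscaled, and they shrink if the early-termination visit supplies the last value or if delivered sessions are costed. Neither the direction nor the size of the net bias in the ratio can be established from the article.

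The conflict between the two EQ-5D rules needs no such assumption about costs; it follows from the two statements in section 2.9. Whether holding the last EQ-5D overstates utility depends on whether the patient later worsens, which the article cannot show. The ODI analysis is unaffected by the economic rule.

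**What to change.** Before analysis, amend the economic part of section 2.9 as follows:

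1. State that last observation carried forward does not apply to costs.
2. Cost trial treatments from sessions actually delivered, with zero after stopping.
3. Impute other missing costs and missing EQ-5D by one model-based method, such as multiple imputation by arm, and add a sensitivity analysis for the missing-data assumption.
4. Use one missing-data rule for EQ-5D in the efficacy and the economic analyses.
5. As an editorial correction, replace the repeated cost category in the perspective sentence and the matching Table 1 footnote so that both agree with the direct medical, direct nonmedical and productivity costs in section 2.8.6.

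The cost is modest extra analysis work and a few sentences of text. With 25 patients per arm the imputation model must be kept small. No later cost or EQ-5D assessment is clearly scheduled for early terminators, so their values after stopping will rest on the model. Collecting them would be a separate change to the protocol.
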